## Abstract

**Background:**

Poor adherence is a major issue and is associated with increased morbidity, mortality, and immense costs for the healthcare system. Due to demographic changes, the burden of neurological diseases is increasing with a crucial exacerbation of the problem of nonadherence. However, comprehensive data on geriatric patients with neurological disorders do not exist to date. In this cross-sectional observational study we aim to identify disease-specific adherence-modulating factors in neurogeriatric patients.

**Methods:**

Patients 60 years or older with neurological disorders will receive an assessment of adherence (Stendal Adherence with Medication Score) and a comprehensive geriatric assessment during their stay in the Department of Neurology or Geriatrics at the Jena University Hospital (baseline data). In addition disease specific data will be derived from medical records. After one and twelve months a telephone interview will be conducted to evaluate if and why changes of medication occurred (follow up data).

**Discussion:**

This study aims to explore disease-specific patterns of nonadherence in elderly patients with neurological disorders and characteristics of information transfer between a specialized center, practicing neurologists, general practitioners, and the patients and their caregivers. This comprehensive data may help to develop and apply complex and disease-specific interventions to enhance adherence.

**Trial registration:**

German Clinical Trials Register DRKS00016774. Registered 19.02.2019.

## Background

The treatment of chronic disorders commonly includes the long-term use of pharmacotherapy and non-pharmacological therapy. However, their full benefits are often not realized because approximately up to 50% of patients either do not take medications as prescribed or do not follow recommendations [1]. In the geriatric population, nonadherence contributes to adverse drug events, increased length of stay and readmissions to hospitals, and a lower quality of life [2, 3]. However, physicians often do not routinely enquire about, and are therefore unaware of the extent of patients´ nonadherence to medication. Factors contributing to nonadherence are numerous [4]. Nonadherence is a dynamic process and may be intentional (when the patient purposefully decides not to follow the recommended treatment) or unintentional (when the patient cannot follow the recommendation) [5]. Not fully understood is why nonadherence often occurs after discharge from hospital. This is probably due to lack of care and routine that was available during patient’s stay in hospital. In Germany, the gap in medical care in hospitals compared to outpatient care is considerable and contributes both to nonadherence and to the frequently observed modifications in the medication regimen after discharge from hospital [6]. This process is influenced by several players and modifiers, such as poor communication, lack of intrinsic involvement of patients, lack of confidence in the physician’s professionalism, and different reimbursement systems. In particular, poor communication between different players in medical care, and feedback from practitioners to the hospital has to date not been sufficiently studied in neurogeriatric patients. This poor communication process may have a strong impact on adherence and patient-reported outcome.

Because the reasons for nonadherence are complex and diverse, interventions to improve adherence must be multifactorial. Although many interventions for increasing adherence have been tested, the best methods to improve adherence still remain unclear [7]. Moreover, the available data are mostly restricted to internal medicine. However, it seems reasonable to assume that the effectiveness of intervention strategies may be disease-specific. Surprisingly, the characteristics of nonadherence in patients with predominant neurogeriatric problems have not been sufficiently characterized, although such disorders – weakness, numbness, poor balance, stroke, Parkinson’s disease, and seizures – become more common with age. Over 20% of adults aged 60 and older suffer from a mental or neurological disorder (excluding headache disorders) and 6.6% of all disability (disability-adjusted life years-DALYs) among adults over 60 is attributed to neurological and mental disorders (WHO Fact sheet 04/2016).

While there are multiple systematic reviews concerning nonadherence in internal medicine (hypertension, COPD, asthma, HIV etc.), little is known about mechanisms of nonadherence in neurogeriatrics [7, 8]. Hence, we aim to collect comprehensive data for adherence and its modifying factors in geriatric patients with neurological disorders. Because drug adherence is a dynamic process, we aim to study a yet underrepresented modifier of adherence: the process after discharge from hospital and attending the outpatient clinic. Our comprehensive data can be used to develop and apply complex and disease-specific interventions to enhance adherence. In parallel we will evaluate the mechanisms of information flow between hospital, practitioner, patient, and caregivers and its impact on adherence and patient-reported outcomes. Therefore, the project will address the following questions:

### Research questions

What are the disease-specific differences and predictors of adherence in neurogeriatric patients?How does the process after patient’s discharge from hospital influence adherence? What are the characteristics of information transfer between a specialized center (university hospital), practicing neurologists, general practitioners, and the patient and their caregivers? What are barriers and facilitators?

### Hypothesis

We hypothesize that nonadherence is also influenced by the underlying neurological disease and that results from patients with arterial hypertension cannot simply be translated one-to-one to neurological disorders. It also seems reasonable that different diseases, such as Parkinson’s disease or epilepsy follow different patterns and predictors for nonadherence. Therefore disease-specific interventions may be more helpful than a general intervention.

## Methods/design

### Setting and participants

Patients 60 years or older with neurological disorders will receive an assessment of adherence, a comprehensive geriatric assessment during their stay in the Department of Neurology or Geriatrics at the Jena University Hospital. Moreover, general data, prescribed medication regime, and disease-specific data about the neurological disorder will be extracted from medical records (baseline data). After one and twelve months a telephone interview will be conducted to evaluate post-discharge changes of medication (follow up data). The planned period of recruitment is from February 2019 to February 2020. The data collection for follow up interviews will take until February 2021.

Inclusion criteria: geriatric patients (defined as age > 60 with multimorbidity OR age > 70) with a common neurological disorder (cerebrovascular disorders, movement disorders, epilepsy, neuromuscular / peripheral neurological disorders).

Exclusion criteria: dementia, acute psychotic symptoms, delirium.

To avoid selection bias all geriatric patients in the Department of Neurology will be screened for eligibility. Known predictors of nonadherence (e.g. depression) will be assessed in detail to avoid bias in the analysis (Table 1).

**Table 1 Tab1:** Specific assessments at baseline

Adherence	Stendal Adherence with Medication Score (SAMS)	18-items addressing reasons for nonadherence
Emotion, Depression	Beck Depression inventory II (BDI)	21-question multiple-choice inventory, for measuring the severity of depression
Mobility - Risk for falls	Timed “Up & Go“	Simple test to assess a person’s mobility and risk of falling
Cognition	Montreal Cognitive Assessment (MoCA)	30-point test assessing several cognitive domains with high sensitivity and specificity for detecting mild cognitive impairment
Personality	Big-Five-Inventory-10 (BFI-10)	10-item scale measuring the Big Five personality traits Extraversion, Agreeableness, Conscientiousness, Emotional Stability, and Openness
Patient physician relationship	Health Care Climate Questionnaire (HCCQ)	Measures outpatients’ experience of communication with physicians
Health-related quality of life	Short Form (36) Health Survey (SF-36)	Widely used 36-item measure of health status. It consists of eight scaled scores, which are the weighted sums of the questions in their section. The lower the score the more disability. The results can be summarized in two main composite scores: the physical composite score (PCS) and the mental composite score (MCS)

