### Recruitment of patients

Eligible participants are continuously recruited by trained study staff during their stay on the ward or during a visit in a specialized outpatient hospital and center (Departments of Geriatrics and Neurology from the Jena University Hospital, Jena, Germany). Because there are no harmful interventions planned, the willingness of patients and caregivers to take part in the study will be high.

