### Data collection

#### Baseline

Data will be collected by trained study staff by applying specific assessments (Table 1) and data will be derived from the routine medical records. The data from the medical records include: general clinical and socio-demographic information, medication regimen, over-the-counter medications, specific information related to neurological disorder: specific disease-severity scales (e.g., Unified Parkinson’s Disease Rating Scale, National Institutes of Health Stroke Scale etc.). Self-administered scores by the patients will be immediately checked for completeness.

Follow up:

Semi-structured follow up telephone interviews with the patients or caregivers will be undertaken one and 12 months after discharge from hospital (up to three attempts to reach the patients). Here, we will ask if there was any change of prescribed medication, if yes why and who undertook the changes of medications. Moreover, the SF-12 and survival rate will be assessed after 12 months. We decided to use a detailed health-related quality of life questionnaire (SF-36) at baseline to better characterize the cohort and a shorter version for the telephone follow up interview because the long version is not practicable in addition to the interview. Both scores (SF-36 and SF12) show a high concordance with each other.

All data will be recorded using pseudonyms in a Windows Access Database.

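### The disease-group comparison mixes newly diagnosed with established patients, although the former can report only medication-taking from before their diagnosis

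*Protocol article*

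**What the plan says.** Setting and participants places the adherence assessment at the index contact: "Patients 60 years or older with neurological disorders will receive an assessment of adherence, a comprehensive geriatric assessment during their stay". SAMS is listed in Table 1, titled "Specific assessments at baseline". Recruitment of patients widens the contact to outpatients: "during their stay on the ward or during a visit in a specialized outpatient hospital and center".

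Apart from the age and multimorbidity rule, eligibility needs only a current diagnosis, "with a common neurological disorder (cerebrovascular disorders, movement disorders, epilepsy, neuromuscular / peripheral neurological disorders". The exclusions are equally short: "Exclusion criteria: dementia, acute psychotic symptoms, delirium". Neither list mentions disease duration, an earlier diagnosis or earlier neurological treatment.

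The telephone interviews at one and twelve months concern medication changes: "Here, we will ask if there was any change of prescribed medication, if yes why and who undertook the changes of medications". SF-12 and survival are added at twelve months. No second SAMS is described.

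The Hypothesis section links the outcome to the disease: "We hypothesize that nonadherence is also influenced by the underlying neurological disease". Sample size aims at a nonadherence estimate per disease subgroup. Statistical analysis models SAMS nonadherence (yes/no) on patient group, demographic factors, disease-specific functional scales, BDI, MoCA and HCCQ. Disease duration and new versus established status are not among the listed variables.

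**The concern.** A person admitted with a first stroke or a first seizure meets the stated criteria. That person's SAMS answers concern medication-taking before the neurological diagnosis, on drugs for other conditions. A person with long-standing Parkinson's disease answers about medication-taking under that disease and its treatment. Both are analysed under their current disease label.

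This affects two analyses. In the between-disease comparison, new-onset patients carry the disease label although the reported behaviour came first, so they give no information on whether the disease influences adherence. In the predictor model, cognition, depression and motor function measured after the event are used to explain behaviour from before it. The article collects severity measures of this kind: "specific disease-severity scales (e.g., Unified Parkinson’s Disease Rating Scale, National Institutes of Health Stroke Scale etc".

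The new-onset share plausibly differs between disorders with sudden onset and disorders that are mostly long-standing at presentation. An apparent disease difference could then be partly a new-versus-established difference, or a real one could be diluted.

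**Working it through.** **Inputs from the article (Sample size):** 250 patients per subgroup, expected nonadherence 25%, two-sided 95% normal-approximation interval, stated precision 5.4 points.

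**Inputs not in the article, assumed here:** the new-onset share f in a subgroup, and the gap d between pre-disease and established nonadherence.

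**1. The plan's own figure.** Half-width = 1.96 × √(0.25 × 0.75 / 250) = 0.0537, or 5.4 points. It reproduces, so the sample size arithmetic is not at fault.

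**2. Shift in one subgroup.** Observed rate = (1 − f) × established rate + f × pre-disease rate. The shift from the established rate is therefore f × d, with the sign of d.

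| Assumed gap d (either sign) | f = 10% | f = 30% | f = 50% | f at which the shift reaches 5.4 points |
|---|---|---|---|---|
| 0 points | 0 | 0 | 0 | never |
| 10 points | 1.0 | 3.0 | 5.0 | 5.4/10 = 54% |
| 15 points | 1.5 | 4.5 | 7.5 | 5.4/15 = 36% |
| 25 points | 2.5 | 7.5 | 12.5 | 5.4/25 = 22% |

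**3. Effect on a comparison of two diseases.** With the same gap in both groups, the difference moves by d × (f in group A − f in group B), so unequal shares are what distort it.

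For illustration, let both groups have an established rate of 25%, with new-onset patients in one group only and a pre-disease rate of 40%. At f = 30% the observed rates are 29.5% and 25%. With 250 per group:
- standard error under no difference = √(2 × 0.2725 × 0.7275 / 250) = 0.0398
- standard error under the stated rates = √((0.25 × 0.75 + 0.295 × 0.705) / 250) = 0.0398
- z = (0.045 − 1.96 × 0.0398) / 0.0398 = −0.83, so a significant difference appears with probability of about 20%

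The same calculation at f = 50% (32.5% against 25%) gives about 46%. The nominal level is 5%. This is an unadjusted two-proportion test, used to show the order of magnitude; it is not the article's mixed model.

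**4. Precision if only established patients are used.** Half-width at 25% = 1.96 × √(0.1875 / n).
- f = 10%: n = 225, 5.7 points
- f = 30%: n = 175, 6.4 points
- f = 50%: n = 125, 7.6 points
- f = 70%: n = 75, 9.8 points

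**The case against.** The study is declared cross-sectional and observational, and its model exploratory. If the aim is to describe nonadherence among patients who present with a given disorder, including new patients is case mix and not bias. This stands for the subgroup proportions taken as descriptions, and it is a reason to keep every patient in the analysis. It does not cover the stated hypothesis of disease influence or the search for disease-specific predictors, both of which need the disease to come before the reported behaviour.

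The article extracts disease-specific information and the medication regimen from records, and a full protocol or SAP may include the date of diagnosis. That is fair as to data collection. But the eligibility criteria and the explanatory variables are stated, and following them as written mixes the two kinds of patient.

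Several stronger readings are tempting and are not supported:
- A reader might infer that the expected 25% is the rate before disease onset. It is the expected rate in the enrolled patients; the article gives no pre-disease rate.
- A reader might infer a known bias larger than the planned precision. Neither the new-onset share nor the gap is given, and the shift may be up, down or nil.
- A reader might infer a cohort of acute admissions only. Outpatients are recruited too. This may lower the new-onset share but does not remove it, since outpatients can also be newly diagnosed.
- A reader might infer from the random effect for time-point that SAMS is repeated. No second SAMS is described, and the two statements should be reconciled.

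The article gives no SAMS recall period. That new-onset patients report pre-diagnosis behaviour is inferred from the timing of the assessment.

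**Conclusion.** The point holds in limited form. As written, the criteria and the model place patients whose reported behaviour preceded the disease alongside patients for whom it did not, and no listed variable separates them. To that extent the between-disease comparison and the predictor model confound disease with new versus established status.

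The size and sign cannot be determined from the article. With a 15-point gap, the shift exceeds the planned precision only above a new-onset share of about 36%, and at a 10% share it is minor. The documents support a change to classification and reporting. They do not support a claim that the subgroup estimates are wrong by a stated amount, or that new-onset patients must leave the main analysis.

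**What to change.** From the medical records already under review, extract date of first diagnosis and any pre-admission neurological medication, and classify each patient as new-onset or established at the index contact. Then:
- keep all patients and report subgroup nonadherence separately by status;
- add status to the explanatory model, with its interaction with patient group where numbers allow;
- specify, before the data are analysed, a sensitivity analysis that repeats the between-disease comparison and the predictor model in established patients;
- interpret the results of new-onset patients as adherence before the disease.

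The cost is one or two record fields, one or two more model terms (more where the interaction is fitted), and wider intervals in the established-only analysis: 6.4 or 7.6 points in place of 5.4 if 30% or 50% of 250 are new-onset. Because nobody is removed from the main analysis, its planned precision is unchanged.

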### Endpoints

The primary outcome is nonadherence according to the Stendal Adherence with Medication Score (SAMS) [5, 9]. We will determine disease-specific predictors of nonadherence in neurogeriatric patients taking personal, environmental and procedural factors into consideration.

### Sample size

The aim is to estimate nonadherence in common neurogeriatric patient subgroups (cerebrovascular disorders, movement disorders, epilepsy, neuromuscular / peripheral neurological disorders). A summary score measuring adherence as percentage is derived from the SAMS as described before [5]. Null percentage is defined as complete adherence. We expect significant nonadherence in about 25% and moderate nonadherence in 50% of the patients. Sample size calculation is based on the precision of our estimate for single proportions using nQuery Advisor 7.0 at 95% confidence interval. When the sample size of one patient subgroup is 250, a two-sided 95% confidence interval for a single proportion using the large sample normal approximation will increase by 5.4% from the observed proportion for an expected proportion of 25% of non-adherent patients.

### Recruitment of patients

Eligible participants are continuously recruited by trained study staff during their stay on the ward or during a visit in a specialized outpatient hospital and center (Departments of Geriatrics and Neurology from the Jena University Hospital, Jena, Germany). Because there are no harmful interventions planned, the willingness of patients and caregivers to take part in the study will be high.

### Data collection

#### Baseline

Data will be collected by trained study staff by applying specific assessments (Table 1) and data will be derived from the routine medical records. The data from the medical records include: general clinical and socio-demographic information, medication regimen, over-the-counter medications, specific information related to neurological disorder: specific disease-severity scales (e.g., Unified Parkinson’s Disease Rating Scale, National Institutes of Health Stroke Scale etc.). Self-administered scores by the patients will be immediately checked for completeness.

Follow up:

Semi-structured follow up telephone interviews with the patients or caregivers will be undertaken one and 12 months after discharge from hospital (up to three attempts to reach the patients). Here, we will ask if there was any change of prescribed medication, if yes why and who undertook the changes of medications. Moreover, the SF-12 and survival rate will be assessed after 12 months. We decided to use a detailed health-related quality of life questionnaire (SF-36) at baseline to better characterize the cohort and a shorter version for the telephone follow up interview because the long version is not practicable in addition to the interview. Both scores (SF-36 and SF12) show a high concordance with each other.

All data will be recorded using pseudonyms in a Windows Access Database.

#### Statistical analysis

Descriptive statistics will be used to describe i) data of the overall study population, ii) clusters of nonadherence, and iii) reasons for longterm changes of prescribed medication. Subjects with missing baseline data will be excluded from analysis. Non-participation will be divided into loss to follow-up (i.e., failure to locate the individual, death) and non-response to the follow-up survey. An exploratory generalized mixed model with random effects (time-point) will be applied to identify possible explanatory factors for nonadherence. We will use nonadherence (yes/no, depending on the SAMS) as dependent variable [5]. Explanatory variables will be patient group (different neurological diseases), age, gender, marital status, education, functional and motor performance (disease specific scales), depression (BDI), and cognition (MoCA), and physician patient relationship (HCCQ). We generally apply a significance level of 0.05 and 2-sided tests.

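### The protocol promises predictors of nonadherence that differ by disease, but its only inferential model names no group-by-predictor interaction or per-disease model and so cannot show it

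*Protocol article*

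**What the plan says.** The Hypothesis section of the protocol article has two limbs. The first concerns levels: "We hypothesize that nonadherence is also influenced by the underlying neurological disease". The second concerns predictors: it considers it reasonable that "different diseases, such as Parkinson’s disease or epilepsy follow different patterns and predictors for nonadherence". From this it argues that interventions tailored to the disease may do better than a general one. Research question 1 covers both limbs: "What are the disease-specific differences and predictors of adherence in neurogeriatric patients". The Endpoints section commits to the second: "We will determine disease-specific predictors of nonadherence in neurogeriatric patients".

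The Statistical analysis section gives one inferential analysis: "An exploratory generalized mixed model with random effects (time-point) will be applied to identify possible explanatory factors for nonadherence". The outcome is binary: "We will use nonadherence (yes/no, depending on the SAMS) as dependent variable". The terms follow: "Explanatory variables will be patient group (different neurological diseases), age, gender, marital status, education", then functional and motor performance on disease-specific scales, BDI, MoCA and HCCQ. The rest of that section's analysis is descriptive: the overall population, clusters of nonadherence, and reasons for long-term medication changes. No interaction with patient group, no stratified analysis and no model per disease appears anywhere in the article.

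**The concern.** A claim that diseases have different predictors is a claim of effect modification: the odds ratio for depression, say, is not the same in epilepsy as in movement disorders. When patient group enters only as one term beside the predictors, each disease gets its own level of nonadherence, but each shared predictor gets a single log-odds coefficient. The quantity that the second limb is about is not in the model.

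That limb carries the protocol's argument for tailored interventions. Run as listed, the analysis would leave it unanswered. A reader could also take a common odds ratio as applying to every disease when it fits none of them. If disease-specific analyses were then added after the data were seen, the choice of predictors to split by disease would be open to selection.

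**Working it through.** **1. Promise against analysis.**

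| Question in the protocol | Term that would answer it | Named in Statistical analysis? |
|---|---|---|
| Does nonadherence depend on the disease? (Hypothesis, first limb) | Patient-group term | Yes |
| Do predictors differ by disease? (Hypothesis, second limb; Endpoints) | Group-by-predictor interaction, or per-disease models that are compared | No |

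**2. Inputs.** The Sample size section gives 250 for one subgroup, 25% nonadherent, and four disease groups. Its own figure reproduces: 1.96 × √(0.25 × 0.75 / 250) = 0.0537, or 5.4 percentage points.

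The following are assumptions and are not in the document: all four groups reach 250 (4 × 250 = 1,000; no total is stated), 25% are nonadherent in each group, each patient contributes one observation, and the effect sizes are as shown.

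**3. A continuous predictor, odds ratio 2.0 per SD in one disease and 1.0 in three.**
- Affected group alone: take a standard normal predictor and set the intercept (−1.21) so that 25% are nonadherent overall. The logistic information per patient, adjusted for the intercept, is E[p(1−p)x²] − E[p(1−p)x]² / E[p(1−p)] = 0.1615 − 0.0515² / 0.1725 = 0.146. Times 250 this is 36.5, so SE = 1/√36.5 = 0.165. The 95% CI is exp(0.693 ± 1.96 × 0.165) = 1.45 to 2.77.
- The shortcut 1/√(250 × 0.25 × 0.75) = 0.146 is right only near an odds ratio of 1. Used at 2.0 it gives 1.50 to 2.66, which is somewhat too narrow.
- Common coefficient: the simple average of the log odds ratios is ln(2)/4 = 0.173, an odds ratio of 1.19. In 1,000 simulated trials the fitted common odds ratio was 1.18, and it was significant at 0.05 in about 60% of them. So the effect is diluted to about 1.2. It does not vanish.

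**4. A binary predictor with effects in opposite directions.** With 50% prevalence and true odds ratios of 0.5, 0.5, 2 and 2, 1,000 simulated trials gave a common odds ratio of 1.00. The predictor was flagged in 5.3% of them, which is no more than the false-positive rate. A 3-df interaction test detected the difference in 98.6%. This pattern is extreme, but it shows that the listed model can miss effect modification entirely.

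**5. What an added interaction could detect.** For a binary predictor, the variance of one group's log odds ratio is 1/(n₀p₀(1−p₀)) + 1/(n₁p₁(1−p₁)). At 50% prevalence this is 0.0853 for an odds ratio of 1 and 0.0900 for an odds ratio of 2, so the weights are 11.72 (three groups) and 11.12. For odds ratios 1, 1, 1, 2:
- weighted mean log odds ratio = 11.12 × 0.693 / (3 × 11.72 + 11.12) = 0.167
- noncentrality = 3 × 11.72 × 0.167² + 11.12 × (0.693 − 0.167)² ≈ 4.06
- power on 3 df at 0.05 = 36%

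| True odds ratios in the four groups | Power, 50% prevalence | Power, 25% prevalence |
|---|---|---|
| 1, 1, 1, 2 | 36% | 31% |
| 1, 1, 2, 2 | 48% | 40% |
| 1, 1, 1, 3 | 74% | 70% |
| 0.5, 1, 1, 2 | 79% | 65% |
| 0.5, 0.5, 2, 2 | 98% | 93% |

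Between two diseases, the ratio of odds ratios detectable with 80% power is exp((1.96 + 0.84) × √(2 × 0.0853)) ≈ 3.2 at 50% prevalence, and about 3.8 at 25%.

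**The case against.** The strongest reply is that the article gives a condensed list of variables. It nowhere says that the model is additive, and interactions are often left to an analysis plan, which is not shown here. It is true that the absence of interactions is read from the list, and a separate plan could supply them. But the article does state the model class, the outcome, the explanatory variables and the significance level, and the analysis so stated does not match the question so stated. That is a mismatch in the text, beyond missing detail.

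A second reply is that the model is labelled exploratory and the study is sized only for the precision of a proportion. This stands, and it lowers the severity. It does not let a model estimate a quantity that it omits.

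Three stronger readings are tempting, and the document does not support them:
- **That the whole hypothesis is untestable.** The patient-group term addresses the first limb and the part of research question 1 about differences between diseases. Only the limb on predictors lacks an analysis.
- **That every predictor is forced to act identically in all four groups.** The list includes disease-specific scales, for which Data collection gives a Parkinson's scale and a stroke scale as examples. These belong to single diseases and cannot share one coefficient without further specification. The point concerns the shared predictors, such as age, BDI, MoCA and HCCQ.
- **That a disease-specific effect would simply be averaged away.** In the one-disease illustration it is diluted and still flagged in about 60% of simulated trials. It disappears only when effects run in opposite directions.

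**Conclusion.** The point holds for the second limb of the hypothesis and for the matching commitment under Endpoints. As listed, the analysis can show that levels of nonadherence differ by disease, but not that shared predictors do. In the illustration the common odds ratio is about 1.2, against about 2.0 (95% CI 1.45 to 2.77) in the one affected disease. The size depends on the assumed 250 per group, 25% nonadherent and the chosen effects. The mismatch itself depends on none of these.

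This should be fixed, but it is not a fatal flaw: the model is exploratory, the design is unharmed, and the same data can answer the question. A reader might infer that adding interactions would settle whether predictors differ. At this size it would not, unless the differences are large.

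**What to change.** In the Statistical analysis section, prespecify patient-group-by-predictor interactions for a short list of shared predictors, for example BDI, MoCA, HCCQ and age, each tested jointly on 3 df. Report the group-specific odds ratios with 95% confidence intervals as the exploratory answer to the disease-specific question, and keep the pooled model for the common effects. Leave the single-disease scales out of this list.

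The change is to analysis wording only and needs no further data or patients. The costs are wider intervals for group-specific estimates, a few more exploratory tests (four with the list above), and low power: about 31 to 36% for a binary predictor with odds ratios 1, 1, 1, 2. The text should therefore state that a non-significant interaction is not evidence that predictors are the same across diseases, and the interpretation should rest on the group-specific estimates and their intervals.
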